## Abstract

**Background:**

One of the most commonly reported problems of randomised trials is that recruitment is usually slower than expected. Trials will cost more and take longer, thus delaying the use of the results in clinical practice, and incomplete samples imply decreased statistical power and usefulness of its results. We aim to identify barriers and facilitators for successful patient recruitment at the level of the patient, the doctor and the hospital organization as well as the organization and design of trials over a broad range of studies.

**Methods/design:**

We will perform two cohort studies and a case-control study in the Netherlands. The first cohort study will report on a series of multicenter trials performed in a nationwide network of clinical trials in obstetrics and gynaecology. A questionnaire will be sent to all clinicians recruiting for these trials to identify determinants - aggregated at centre level - for the recruitment rate. In a case control-study nested in this cohort we will interview patients who refused or consented participation to identify factors associated with patients' consent or refusal. In a second cohort study, we will study trials that were prospectively registered in the Netherlands Trial Register. Using a questionnaire survey we will assess whether issues on hospital organization, trial organization, planning and trial design were associated with successful recruitment, i.e. 80% of the predefined number of patients recruited within the planned time.

**Discussion:**

This study will provide insight in barriers and facilitators for successful patient recruitment in trials. The results will be used to provide recommendations and a checklist for individual trialists to identify potential pitfalls for recruitment and judge the feasibility prior to the start of the study. Identified barriers and motivators coupled to evidence-based interventions can improve recruitment of patients in clinical trials.

## Background

Evaluation research is essential to inform evidence based health care decisions. The randomized controlled trial (RCT) is worldwide considered as the best instrument to evaluate the effectiveness of medical interventions. One of the most commonly reported problems with the conduct of such RCTs, however, is that recruitment is usually slower than expected. In the 1970's an American pharmacologist, Luis Lasagna, stated that once trial recruitment starts, the supply of eligible patients becomes a fraction of what was assumed before the start of the trial. This phenomenon, currently known as Lasagna's Law, still holds today [1,2]. In the UK, in a cohort of 114 multicenter trials funded by the UK Medical Research Councel and the UK Health Technology Assessment Programme between 1994 and 2002, less than one-third recruited their original target within the time originally planned, and around one third had extensions [1].

If in a clinical trial the targeted sample size is not achieved, it will have less statistical power to convincingly demonstrate potentially important differences between the groups, which might make the results less useful or not at all applicable in clinical practice - it will not improve practice and wastes the contribution of participants who already participated. In addition, if recruitment has to be extended to reach the required sample size, the trial will cost more and take longer, thus delaying the use of its results in clinical practice. As the total amount of funding is limited, fewer trials can be conducted and hence less clinical dilemmas can be solved.

Reasons for lack of recruitment can be found at different levels: the patient, the doctor, the participating centre or department, the study organisation and the study design (see figure 1) [1,3-7].

**Figure 1 F1:**
[figure not shown]
**Factors for lack of recruitment can be found on different levels: with interactions between levels**.

Rendell et al. reviewed incentives and disincentives to participation, focussing on participation of clinicians [6]. Lovato et al. and Ross et al. reviewed barriers to both patient and clinician participation [4,8]. Other reviews were dedicated to a specific disease or group of diseases [3,9-13]. Frequently mentioned barriers for patients are preference for one form of treatment, concerns with the trial setting, dislike of randomisation, general discomfort with the research process, distrust in researchers, complexity and stringency of the protocol, presence of a placebo or no-treatment group, potential side effect, fear that trial involvement would have a negative effect on the relationship with their physician and their physicians attitudes towards the trial, the potential for increased demands and the mere inability to make a decision [13,14]. Frequently mentioned barriers to clinician participation are time constraints, lack of staff and training, worry about the impact on doctor-patient relationship, concern for patients, loss of professional autonomy, difficulty with the consent procedure, lack of rewards and recognition, and an insufficiently interesting question [4].

These reasons might be different across specialties, countries or due to the nature of the disease or disease population, but will probably also have common denominators [10]. In many of the included papers in the reviews it is uncertain if and how these results can be generalized to other trials and populations. In the reviews there might also be an over representation of very successful or very unsuccessful recruiting trials, as especially these trials might invoke a study of determinants of recruitment by the trial coordinator. Recently, the STEPS study focused on recruitment from different perspectives, and although they identified determinants, they did not have sufficiently definitive results to make strong recommendations [1].

In conclusion, although several potential barriers have been identified, it remains unclear whether they are applicable for any next trial. At present, neither a rule which can predict successful recruitment, nor a checklist to assess the feasibility of recruitment prior to the start of a trial, or even prior to a funding decision, is available. We therefore aim to study methods for IMproving PArticipation in Clinical Trials (IMPACT). We aim to identify predictors for (un)successful patient recruitment at the level of the patient, the doctor and the study and organizational level in order to provide a rule or checklist for successful patient recruitment in clinical trials.

## Methods/design

To address this topic at different relevant levels, we plan two cohort studies and a nested case control study in The Netherlands. In the first cohort study we will focus on successful recruitment at the level of participating centres, where characteristics of the clinician will be aggregated at the level of the centre. In a case control study embedded in this cohort study we will focus on the patient level. In the second cohort study we will identify determinants for success of recruitment in a cohort of trials registered in the national Netherlands Trial Register.

This study did not require formal approval of an ethics committee or internal review board, as was confirmed by the ethics committee of the Academic Medical Center. We interpreted completion and return of a questionnaire as the respondent's consent for participation. Methodological details of these studies are described below.

### Cohort study 1: predicting recruitment at centre level

The first cohort aims to determine which factors on centre level will influence recruitment of patients. The cohort will consist of a series of multicenter trials performed in a nationwide Consortium on studies in Obstetrics and Gynaecology, in which currently over 70 medical centres participate (table 1) [15]. At the centre level, we will study aspects of the doctor as well as aspects of the organisation. A questionnaire will be sent to gynaecologists, residents, research nurses, and midwives in the Netherlands who work in centres recruiting for these trials. We will also collect data on characteristics of clinicians and study organization.

**Table 1 T1:** A cohort of studies performed in a nationwide Consortium on studies in obstetrics and gynaecology in the Netherlands.

Nr	Trial	Population	Sample size
**1**	Amphia	Women with a multiple pregnancy before 20 weeks pregnancy	720

**2**	Hypitat II	Women with pregnancy induced hypertension or mild pre-eclampia at 34-37 weeks gestation	400

**3**	Digitat	Women with a singleton pregnancy at 36 completed weeks of gestation or more	626

**4**	Ppromexil	Women with preterm prelabour rupture of membranes between 34 and 37 weeks gestation	520

**5**	Stan	Women in labour over 36 weeks of gestation with an indication for CTG monitoring	2400

**6**	Apostel 1	Women with threatened preterm labour at 24-34 weeks gestation.	220

**7**	Apostel 2	Women with threatened preterm labour at 26-32+2 weeks gestation.	400

**8**	TRIPLE P	Women with a singleton pregnancy	1920

**9**	Probaat	Women ≥ 37 weeks of gestation and Bishop score < 6	812

**10**	PreCare	Women with preeclampia or HELLP in previous pregnancy	250

**11**	WOMB	Women with >1000 mL postpartum fluxus	400

**12**	Truffle	Women at 26-32 weeks gestation with a fetus with intrauterine growth retardation.	500

**13**	Allo	Women with suspected fetal asphyxia during labour	220

**14**	ProTWIN	Women with a multiple pregnancy between 12 and 20 weeks gestation	660

**15**	Metex	Women with an extra uterine gravidity	72

**16**	ESEP	Women with an extra uterine gravidity in one of the tubae and a normal contralateral tuba	450

**17**	INeS	Couples with unexplained subfertility or a mild male factor	600

**19**	MOVIN'	Women with anovulation not pregnant after 6 ovulatory cycles of clomid	200

**20**	Bedrest	Women who undergo intra-uterin insemination	250

**21**	VUSIS 1	Women with stress-incontinence	100

**22**	PORTRET	Women with stress incontinence aged 35-80 years	400

**23**	CUPIDO	Women with vaginal prolaps	114

**24**	Pompoen	Women with postmenopausal bleeding	200

Based on these data, we will construct a prediction model. The primary outcome will be the percentage of eligible patients recruited, defined as the number of randomized patients per centre divided by the number of eligible patients. Secondary outcomes will be the number of randomized patients divided by the number of available patients per centre stratified per study. The number of eligible patients is registered for a part of the studies and will be estimated based on the LVR, the Dutch national perinatal registry.

As potential predictors we will take into account characteristics of the clinicians, e.g. the proportion of doctors with a PhD, as well as clinicians' views on the trial, e.g. prior belief in the relevance and quality of the study design. We will also collect characteristics of the study organisation: e.g. status of the hospital (academic, teaching or general), availability of research nurses or employees for counselling of the studies, clarity of research protocol and logistics, responsibilities for recruitment. These potential predictors reflect clinicians' views on these topics, aggregated at the level of department.

For reliable modelling on prediction experts recommend that there should be at least about 10 events in the data set for each potential predictor to be included in the model [16]. As we expect a response in about 65 of 70 centres, prediction models can include about 6-7 predictors at centre level.

Missing values will be imputed. The predictive accuracy of the model will be assessed using calibration, which evaluates the correspondence between the model's predicted percentage of randomized patients and the observed percentage of randomized patients. The discriminative ability of the prognostic model will be assessed by using receiver operating characteristics (ROC) analysis. We will then perform internal validation using bootstrapping and apply shrinkage to correct for over fit. A simplified prediction rule will be derived from the regression coefficients of the independent predictors in the multivariable model. If a valid prediction rule cannot be constructed, we will use the multivariable model to identify risk factors for a low recruitment percentage.

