Another strong point is that the first cohort is based on clinicians recruiting for a set of trials from the nationwide consortium in Obstetrics and Gynaecology. All academic medical centres and the majority of the Dutch hospitals recruit for trials running in this consortium, which enables us to cover a large part of the Netherlands without selection of the explicitly research minded hospitals. Moreover, the second cohort of studies from the Dutch Trial Register will be a representative sample of all trials performed in the Netherlands, since from July 2005 registration is required for publication in important journals. It will be a challenge to deliberately handle the heterogeneity of the trials included.

There are also some limitations in this study which require a remark. First, although we focus on different levels (level of the patient, centre and study) it is not possible to directly link the data from these levels. We therefore cannot disentangle the relative impact of each level to the recruitment problems. However, we will be able to provide a satisfactory estimation, given the variability between different specialties and trials.

Second, as we focus on trials in obstetrics and gynaecology in the first cohort study, generalisability of these results to other clinical specialties should be evaluated. As in this study it is not feasible to survey all specialties in depth, we think it is more informative to have a complete picture of one specialty over a limited amount of information from many specialties.

Furthermore, in the second cohort on predicting successful recruitment on study level, the predefined recruitment target will probably - as most power calculations - be based on limited information. When information emerges from external sources or interim analyses, the sample size might be adapted, which can make the trial more successful or efficient without reaching the originally planned sample size. However, sample size targets are taken into account when funding decisions are made. The extent to which a trial meets initial expectations can be viewed as a legitimate marker of trial success. Moreover, recruitment can be viewed of as a surrogate marker of more significant markers of success, such as the extent to which the trial question has been successfully addressed [1].

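### Cohort 1's primary outcome pools all trials into one percentage per centre with no stated adjustment for trial mix, so centre comparisons are confounded by which trials each centre runs

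*Protocol article*

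**What the plan says.** All of the following is in the Protocol article, mostly under *Cohort study 1: predicting recruitment at centre level*.

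- **Aim:** "The first cohort aims to determine which factors on centre level will influence recruitment of patients".
- **Primary outcome:** a percentage "defined as the number of randomized patients per centre divided by the number of eligible patients".
- **Secondary outcomes:** "Secondary outcomes will be the number of randomized patients divided by the number of available patients per centre stratified per study". Stratification by study appears only here, and the denominator word changes from eligible to available.
- **Source of the denominator:** "The number of eligible patients is registered for a part of the studies and will be estimated based on the LVR", the national perinatal registry.
- **Setting:** a "nationwide Consortium on studies in Obstetrics and Gynaecology, in which currently over 70 medical centres participate". Table 1 lists 23 trials (numbered 1 to 24, without 18) in obstetrics, subfertility and gynaecology.
- **Predictors:** features of the clinicians and of the organisation (hospital status and availability of research nurses are examples), and also "clinicians' views on the trial, e.g. prior belief in the relevance and quality of the study design". All are aggregated by department.
- **Model size:** 6 to 7 predictors, from about 65 responding centres out of 70.

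The Discussion allows that participation may depend mainly on features peculiar to each trial and its population.

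**The concern.** A percentage pooled over trials is a weighted average of trial-specific rates. The weights are the numbers of eligible patients a centre happens to have in each trial. Two centres can recruit equally well in every trial they share and still score differently, because their weights differ.

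The aim is to find centre features that influence recruitment. If academic centres, or centres with research nurses, tend to run a different set of trials, the easy or difficult nature of those trials will be credited to the centre feature, or will hide a real effect. The prediction rule, the fallback list of risk factors and the checklist promised in the Discussion would all inherit this.

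A related loss affects clinicians' views on a trial. A department's opinion of one trial, averaged with its opinions of others, is no longer tied to recruitment in the trial it concerns.

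**Working it through.** **1. Unit of analysis.** The plan's own figure reproduces with one record per centre: 65/10 = 6.5 and 70/10 = 7.0, hence 6 to 7 predictors. Records by centre and trial would be more numerous. Together with the contrast between the primary and secondary definitions, this shows that the primary outcome is pooled over trials.

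**2. Variety of trials.** The Table 1 sample sizes sum to 12,434 over 23 trials. They run from 72 to 2400, a ratio of 33. The two largest trials account for 2400 + 1920 = 4320, or 35%.

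**3. Two centres, identical recruitment within each trial.** The rates are assumed, since the article gives none. Centre A's eligible patients split 80:20 between trials 1 and 2, and centre B's split 20:80. The pooled percentage is (share in trial 1 × rate 1) + (share in trial 2 × rate 2).

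| Rate 1 / rate 2 | Centre A | Centre B | Gap (points) |
|---|---|---|---|
| 45% / 40% | 44% | 41% | 3 |
| 50% / 30% | 46% | 34% | 12 |
| 60% / 20% | 52% | 28% | 24 |
| 70% / 10% | 58% | 22% | 36 |

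Stratified by trial, the gap is 0 in every row.

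**4. The order can reverse.** Let B be 5 points better than A in both trials (65% and 25% against 60% and 20%). Pooled, B scores 0.2 × 65 + 0.8 × 25 = 33%, and A scores 0.8 × 60 + 0.2 × 20 = 52%.

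**5. How much of the outcome is still centre performance?** A simulation used 65 centres, Table 1 sizes as weights and a true centre effect with SD 0.5 on the logit scale. The table gives the share of variance in the pooled percentage explained by the true centre effect.

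| Each centre runs | Between-trial SD 0.25 | SD 0.5 | SD 1.0 |
|---|---|---|---|
| every trial | 0.99 | 0.98 | 0.93 |
| about half | 0.97 | 0.89 | 0.69 |
| about a quarter | 0.93 | 0.79 | 0.49 |

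**6. False positives for hospital status.** These simulations had 65 centres, 12 of them assumed academic, Table 1 sizes as weights, no centre effect and a nominal 5% test.

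- Over a span of strengths for the link between status and portfolio (2000 runs per setting), rejection was 5-10% when trial rates spanned 10 points, 5-26% at 30 points and 5-30% at 50 points. After standardising by trial it was 4-5% throughout.
- A second set (1500 runs, each trial run by about half the centres) varied the link as a logit slope of 0, 0.5, 1 and 2. With trial rates of 10-60%, rejection was 6%, 10%, 17% and 28%. With rates of 25-45% it was 5%, 5%, 8% and 12%.

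**The case against.** The strongest reply is that the outcome already divides by eligible patients, so centre volume and trial size alone do not drive it, and that the per-study secondary outcomes provide a check. Both are true. The check is partial, because it is secondary and its denominator is worded differently.

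A second reply is that nothing in the article shows trial mix to be large or linked to any predictor. That stands as a limit on the size of the problem. It does not remove it, since the Discussion itself allows that trial-specific features may predominate.

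A third is that centre-by-trial denominators may be poor, being registered for only some trials. This applies equally to the plan as written, because the pooled denominator has to be built from the same trial-level counts.

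A full analysis plan might add a trial term, but the primary outcome and the unit of analysis are fixed in this article.

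Four stronger readings are tempting and not supported:

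- *The outcome measures portfolio instead of recruitment.* It measures both. In all but the most extreme setting of step 5 the centre effect still explains most of the variance.
- *TRIPLE P, with its very wide population label, swamps the denominator.* This is possible, but the label is one line of shorthand and the eligibility criteria are not shown.
- *Women are counted twice in Amphia and ProTWIN, or in Apostel 1 and 2.* This is also possible, but it requires both trials to be open in the same centre at the same time, and Table 1 gives no dates.
- *The Discussion is wrong that "it is not possible to directly link the data from these levels".* That sentence concerns linking patient, centre and study data, which come from different substudies. Separating trial from centre within cohort 1 does not contradict it.

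**Conclusion.** The point holds as one of confounding by trial mix. The primary outcome is pooled over trials, no adjustment is stated, and the split by study is left to secondary outcomes with a different denominator word.

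The size cannot be fixed from the article. It depends on how far recruitment rates differ between trials, how far portfolios differ between centres, and how closely portfolio follows a predictor. Under the assumptions shown, the false-positive rate for hospital status ranges from the nominal 5% (no link, or similar trial rates) to about 30% (strong link, rates of 10-60%). Trial mix takes from almost none to about half of the variance in the outcome. Associations with hospital status or research nurses may therefore be spurious or masked; it does not follow that they will be.

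**What to change.** Make the centre-by-trial count the unit of the primary analysis: randomised out of eligible, in a binomial mixed model with trial effects and a random centre effect. At the least, replace the pooled figure with a trial-standardised centre percentage. Use the same eligible denominator for primary and secondary outcomes. Keep organisational features at centre level, and enter views on a trial at centre-by-trial level where the questionnaire records them per trial; the article does not say whether it does.

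The cost is one reworded outcome and a slightly more complex model. Little or no new outcome data should be needed, because the per-study secondary outcomes already call for counts by centre and trial. Some trial-specific denominators will be registry estimates, and a binomial model treats them as known. That weakness is already present in the pooled outcome and should be acknowledged in either case.

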### Cohort study 2: Predicting recruitment success of trials registered in the Netherlands Trial Register

In a second cohort study, we will include study trials that have been registered prospectively in the Netherlands Trial Register. The cohort of studies will consist of all studies that registered their stop date between January 1^st ^2005 and January 1^st^, 2010 (expected number of available trials N≈1000). Using a questionnaire survey, we will investigate whether issues on hospital organization, trial organization, planning and trial design are predictive for successful recruitment, defined as ≥80% of the patients recruited within the time frame defined in the grant application.

As potential predictors we will take into account trial characteristics, i.e. placebo arm, blinding, experimental status of the intervention to be evaluated; characteristics of the trial organisation, i.e. research staff available to counsel patients and acquire follow up data, who is responsible for recruitment; and characteristics of the principal investigator and the research group, i.e. composition of different expertise, experience and training in trial research. For reliable prediction modelling experts recommend that there should be at least about 10 events in the data set for each potential predictor to be included in the model [16]. In a sample of 1000 studies, with a (low) recruitment rate of 30% about 30 potential predictors can be tested reliably.

Missing values will be imputed. Like in the cohort study I, the predictive accuracy of the model will be assessed using calibration, which evaluates the correspondence between the model's predicted probabilities of recruitment success and the observed recruitment success over groups. The discriminative ability of the prognostic model will be assessed by using receiver operating characteristics (ROC) analysis.

We will perform internal validation using bootstrapping and apply shrinkage to correct for over fit.

A prediction rule will be derived from the regression coefficients of the independent predictors in the multivariable prognostic model. If a valid prediction rule cannot be constructed, we will use the model to identify risk factors for a low recruitment percentage.

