## Discussion

At the end of the study, we will have an inventory of predictors, barriers and facilitators for successful patient recruitment in trials. The first cohort study will provide information on prediction of recruitment in different centres participating in obstetrical, subfertility and gynaecological trials. From the nested case-control study we will obtain qualitative and quantitative information about factors which influence patient participation. The second cohort study will provide insight in factors related to successful recruitment at study level. Based on the prediction models or risk factors for unsuccessful recruitment, we will develop a set of recommendations and a checklist that can be used by individual trialists before the start of the study to assess if recruitment of the proposed sample size with their strategy will be feasible.

A strong point of the design is that we will address recruitment factors at different levels and from different perspectives, throughout a variety of trials in various fields of medicine. This will provide us with a broad overall picture of reasons why patients participate or refuse participation, and will provide insight in a common denominator between trials, or clarify differences. At the same time this is a potential pitfall: the reasons for participation or non-participation in a clinical trial might predominantly depend on exclusive characteristics of a trial and its targeted population, so that general predictors may not be identified. If so, the results are still valuable, but we should focus on the development of a general applicable recruitment tool. Such a tool might consist of a strategy based on interviewing a number of eligible participants as well as a number of recruiters and/or clinicians prior to start or during the piloting of the trial.

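### In cohort 1, clinicians' views gathered while their centres are already recruiting enter a model that feeds a checklist meant for use before a trial starts

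*Protocol article*

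**What the plan says.** All references are to the protocol article.

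- **Predictors.** The section on cohort study 1 names characteristics of the clinicians, such as the proportion of doctors with a PhD, and also "clinicians' views on the trial, e.g. prior belief in the relevance and quality of the study design". It adds organisational items: hospital status, research nurse availability, clarity of protocol and logistics, and responsibility for recruitment. It then says: "These potential predictors reflect clinicians' views on these topics, aggregated at the level of department".
- **Timing.** The questionnaire goes to staff "who work in centres recruiting for these trials". The Abstract agrees ("A questionnaire will be sent to all clinicians recruiting for these trials"), and so does the Discussion ("the first cohort is based on clinicians recruiting for a set of trials from the nationwide consortium"). No measurement of views before a centre opens is described.
- **Outcome.** The primary outcome is the share of eligible patients randomised in each of the same centres.
- **Use.** Regression coefficients become a simplified prediction rule. If no valid rule emerges, the same model is read for risk factors. According to the Discussion, the models or risk factors lead to a "checklist that can be used by individual trialists before the start of the study". The Background names the same purpose and extends it to the time before a funding decision.
- **Safeguards.** Calibration, ROC analysis, bootstrap validation and shrinkage are planned. The limitations cover unlinked levels, generalisability, adapted sample size targets, the Dutch setting and selective response. They do not mention hindsight or reverse causation.

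**The concern.** A predictor for use before a trial starts should be measured as it would be at that moment. Here a view described as prior is recorded once the centre has experience of recruiting. A department that struggles may call the protocol unclear, or the question less relevant, because it struggled. The association would then run at least partly from outcome to predictor.

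Two things are at stake. First, the accuracy reported for the rule may not carry over to pre-start use, where staff have no recruitment experience to colour their answers. Second, the article allows the cohort 1 model only about 6-7 predictors, so one contaminated item could take the place of a genuine one. The checklist could then direct trialists to symptoms of poor recruitment.

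The planned internal validation cannot detect this. Bootstrapping and shrinkage deal with overfitting to a finite sample. Every resample contains the same contaminated ratings, so the optimism-corrected performance would still include the hindsight component.

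**Working it through.** **The plan's own figure.** With 65 responding centres and ten per predictor, 65/10 = 6.5, which matches the stated 6-7. This figure is not in dispute. It shows how little room the model has.

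**Timing against use.**

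| Item | When its value is fixed | Available before start in the same form? |
|---|---|---|
| Hospital status, proportion of doctors with a PhD | Before recruitment, and checkable | Yes |
| Research nurse availability | Can be fixed as at centre opening | Yes, if taken at opening |
| Belief in relevance and design quality | Asked in centres already recruiting | No: a recalled or current view |
| Clarity of protocol and logistics | Asked in centres already recruiting | No: a current view |

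**Illustration of size.** The document gives no value for hindsight, so the two parameters below are assumptions.

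- B is the true prior belief of a centre, standardised.
- Y is the centre's recruitment, standardised.
- r is the true correlation between B and Y.
- g is the hindsight shift in the rating, in SD of belief per SD of recruitment.
- The reported rating is R = B + gY.

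Then corr(R, Y) = (r + g) / √(1 + 2gr + g²).

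With no true relation (r = 0):
- g = 0.25: 0.25/√1.0625 = 0.24
- g = 0.5: 0.5/√1.25 = 0.45

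With r = 0.3:
- g = 0.25: 0.55/√1.2125 = 0.50
- g = 0.5: 0.80/√1.55 = 0.64

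A simulation of 65 centres (4,000 runs, two-sided 5% test of the correlation) gave, for r = 0:

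| g | Mean correlation | Runs significant |
|---|---|---|
| 0 | 0.00 | 4.7% |
| 0.25 | 0.24 | 49.5% |
| 0.5 | 0.44 | 96.7% |

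The formula value for g = 0.5 is 0.447 and the simulated mean 0.444.

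**Hand check.** For a correlation of 0.2425, t = 0.2425 × √(63/(1 − 0.0588)) = 1.98. This lies next to the critical value of 1.998, so about half of the runs should be significant, as found.

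**The case against.** The case on the other side has four parts.

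1. **Knowledge of the outcome is not stated.** The article gives no questionnaire date relative to each trial's recruitment. The denominator of the outcome is registered for only part of the studies and is otherwise estimated from the national perinatal registry. Respondents may sense progress without knowing their centre's percentage. This stands. A reader might infer that staff answer after recruitment has ended and know the final result, but for cohort 1 the text supports only that recruitment is under way. The point needs no more than that, since experience of slow progress is enough to colour a rating.

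2. **The item is labelled prior.** It may be meant as a recalled view, with wording left to the full protocol. The Discussion also envisages, as a fallback tool, interviewing recruiters before the start or during piloting. But a recalled view is open to the same hindsight, and the fallback interviews are not the data that the model is fitted to.

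3. **Cohort 2 is different.** A reader might extend the point to cohort 2, because its trials are selected by a registered stop date ("The cohort of studies will consist of all studies that registered their stop date between January") and surveyed by questionnaire. The documents do not support this. The predictors listed there are essentially factual: placebo arm, blinding, experimental status, research staff, responsibility for recruitment, and the team's expertise, experience and training. A calculation with a rating item in about 1000 trials would therefore describe an item that the article does not list, and would greatly overstate the strength of the signal. In 65 centres split 33/32 (an assumption), a hindsight difference of 0.5 SD gives z = 0.5/√(1/33 + 1/32) = 2.0, and 0.3 SD gives 1.2.

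4. **Views are a stated object of study.** Leaving them out of the rule loses something the investigators want to learn. This is fair, and it is why they should be kept in a second model and not discarded.

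**Conclusion.** The point holds for cohort 1. Opinion items are measured in centres already recruiting, are modelled together with pre-start facts, and feed a rule and checklist for use before a trial starts. The planned validation does not address the mismatch, and the limitations do not mention it. The fallback of reading risk factors from the same model has the same weakness.

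Neither the size nor the direction of the bias can be determined from the document. That slow recruitment lowers the ratings is plausible but assumed. Under that assumption, with no true relation and 65 centres, modest shifts of 0.25 to 0.5 SD per SD of recruitment are enough to give correlations of about 0.24 to 0.45. These figures show what could happen and do not estimate what will. Factual items are much less exposed. The surveys remain useful for describing associations. What needs correcting is the use of the opinion items in a pre-start rule.

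**What to change.** In cohort 1:

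- Derive the pre-start rule only from centre-level items that are fixed before recruitment opens and can be checked against records, for example hospital status, research nurse availability at opening, and the proportion of doctors with a PhD.
- Fit a second model that adds the opinion items. Report it as association only, show its gain in performance separately, and keep that gain out of the accuracy claimed for the rule.
- State in the limitations that views were collected in recruiting centres and may reflect experience of recruitment.
- Apply the same separation if the fallback to risk factors is used.

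No change is needed to the predictors listed for cohort 2 on this ground.

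The cost is one extra model on data that are collected anyway. The rule will have fewer items and may show lower apparent accuracy. The second model must also respect the limit of about 6-7 predictors, so the number of opinion items added has to be restricted.
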